### Sample size calculation

Sample size was calculated based on anticipated changes in body fat using data from our previous study of prebiotic fibre supplementation in overweight and obese adults [13]. The expected change in body fat in the pulse fibre group is -1.11 kg whereas the expected weight change in the control group is +0.20 kg, with a standard deviation of ±1.6 kg. Assuming an alpha = 0.05 and power = 0.80 (80%) we would need to recruit 24 subjects in each study arm. An additional 6 patients per group will be added to account for the expected 20% loss to follow up for a total of 30 patients per group.

### Statistical analysis

Data will be analyzed using SPSS statistical program (IBM Software, Armonk, NY) with results considered statistically significant (2-sided) at P ≤ 0.05. Values with skewed distribution will be logarithmically transformed prior to analysis. Baseline characteristics will be compared between groups using chi-square for categorical variables and *t* tests for continuous variables. Primary analysis will be performed on an intent-to-treat basis, regardless of subject compliance. The primary outcome measure is change from baseline to 12 weeks in body fat. ANCOVA, with testing for confounding factors (sex) and potential covariates (BMI, age) will be used to assess the difference between groups at weeks 0 and 12. Should the main effect of diet be significant, Tukey’s multiple comparison test will be used. Secondary outcomes measured at 0 to 12 weeks (e.g. satiety hormones, glycemia, insulinemia, food intake) will be analyzed with ANCOVA as above. For variables measured over time (e.g. body weight, satiety hormones and glucose at 0, 30, 60, 120 and 180 minutes), a mixed model of repeated measures ANCOVA will be applied to examine the effect of treatment, time and their interaction. Our planned secondary analysis will be per protocol with all subjects who complete the 12 week intervention and are compliant based on consumption of ≥80% the product doses. Cases with missing outcome data will be excluded from analysis.

For metabolomics analysis, in addition to univariate tests, multivariate analysis will conducted using SIMCA-P + 12.0.1 software (Umetrics, Sweden). Data will be reprocessed by mean-centering and unit variance scaling. A supervised partial least squares discriminant analysis (PLS-DA) approach will be used to compare the variance of metabolite concentrations between the two sample classes (diet: control and pea fibre). A supervised orthogonal partial least squares analysis will be used (control versus pea fibre) for a direct comparison of the variance between diet type (Y variable) and metabolite concentrations (X variable). The results from the metabolomics analysis will also be combined with the plasma satiety hormones and other biological measurements and regressed to the diet type using O2-PLS-DA (orthogonal PLS-DA).

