The overall study design is described in Figure 1, and the outcome measures are described individually below. Anthropometric data (weight, BMI, waist circumference) and food intake (3-day weighed food record) will be collected at baseline and at 4 week intervals. Subjective ratings of appetite will be measured using validated visual analogue scales (VAS) by the subjects at home on a weekly basis. At baseline and follow-up (12 weeks), body composition will be measured by DXA, and an oral glucose tolerance test will be performed to assess glucose tolerance. Plasma inflammatory markers (including TNF-α and CRP), lipids (total, LDL- and HDL-cholesterol, and triglyceride), and satiety hormones (including GLP-1, PYY, ghrelin and leptin) will be measured using methods already established in the laboratory and described below. Subjects will be provided with an *ad libitum* lunch buffet to measure objective food intake. Serum samples will undergo metabolomics analysis using proton nuclear magnetic resonance spectroscopy (^1^H-NMR) [39]. ^1^H-NMR will allow us to measure global metabolic responses which will complement the plasma biomarkers concurrently measured. Stool samples will be collected for analysis of gut microbiota and for fecal water metabolomics using ^1^H-NMR.

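### The primary analysis is called intent-to-treat, but the stated rule on missing outcomes makes it an available-case analysis of about 48 of 60 randomised participants

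*Protocol article*

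**What the plan says.** The Statistical analysis section sets the analysis population in one sentence: "Primary analysis will be performed on an intent-to-treat basis, regardless of subject compliance". The outcome follows: "The primary outcome measure is change from baseline to 12 weeks in body fat". It is compared between arms by ANCOVA on weeks 0 and 12. A repeated-measures mixed model is kept for variables measured over time, such as body weight.

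The secondary analysis is then defined: "Our planned secondary analysis will be per protocol with all subjects who complete the 12 week intervention and are compliant", with compliance meaning at least 80% of the product doses. The paragraph closes with "Cases with missing outcome data will be excluded from analysis". That sentence names no particular analysis or outcome.

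Two other sections bear on this. Design, participants, and setting gives the timing of the primary measurement, "At baseline and follow-up (12 weeks), body composition will be measured by DXA", and of the interim data, "Anthropometric data (weight, BMI, waist circumference) and food intake (3-day weighed food record) will be collected at baseline and at 4 week intervals". Sample size calculation states the loss that the investigators expect: "An additional 6 patients per group will be added to account for the expected 20% loss to follow up".

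**The concern.** An intent-to-treat analysis keeps every randomised participant in the arm to which they were assigned. A rule that removes anyone without an outcome does not, and the article defines no modified intent-to-treat set that would reconcile the two.

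The rule matters most for the primary outcome. Fat mass has no interim value, and the primary model is not a repeated-measures model. A participant without a week-12 scan therefore contributes nothing to the primary comparison, even if baseline fat mass and weight at weeks 4 and 8 are on file. Those weights do enter the separate body-weight model, so they are unused only for fat mass.

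Two things are at stake. The report would attach the intent-to-treat label to an available-case estimate. And the balance created by randomisation is guaranteed only for all 60 participants, not for those who return for the scan. The article itself expects that a rapid rise in fibre intake can cause gut discomfort, and raises the dose in steps for that reason. A reason for leaving that is tied to one arm is therefore conceivable, although no section says that people will leave for it.

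**Working it through.** **Inputs** (Sample size calculation, Statistical analysis, Design): change of -1.11 kg with fibre and +0.20 kg in control, both taken here as change in body fat; SD 1.6 kg; two-sided alpha 0.05; power 0.80; 30 per arm; 20% loss.

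**1. The plan's own figures.**
- Difference = 1.11 + 0.20 = 1.31 kg.
- n per arm = 2 × [1.6 × (1.960 + 0.842) / 1.31]² = 23.42, rounded up to 24.
- Allowing for loss: 24 / (1 − 0.20) = 30.

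Both stated figures reproduce. A t-based calculation gives 24.4, so 25, which is close enough to raise no issue.

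**2. Size of the primary set under the stated rule.**
- Excluded: 0.20 × 60 = 12.
- Analysed: 60 − 12 = 48, or 24 per arm.
- Power at 24 per arm is 81.0% (normal) or 79.3% (t), so the inflation does its job for precision.

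**3. Who is in each set.**

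| Participant | Primary set as written | Per-protocol set |
|---|---|---|
| Completes, at least 80% of doses, scanned | in | in |
| Completes, below 80% of doses, scanned | in | out |
| Stops the biscuits, attends the week-12 scan | in | out |
| No week-12 scan | out | out |

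The two sets differ by both completion and the dose threshold. What separates the primary set from a true intent-to-treat set is the last row.

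**4. Illustration of possible bias.** The documents give no outcome for those lost, so this step rests on assumptions. The observed difference is taken as 1.31 kg, loss is 20% in each arm, and control-arm losses change like the observed controls. Let k be the share of the 1.31 kg benefit that fibre-arm losses keep.

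All-randomised difference = 0.80 × 1.31 + 0.20 × k × 1.31

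| Fibre-arm losses | k | All-randomised difference | Overstatement |
|---|---|---|---|
| Resemble those observed | 1 | 1.31 kg | 0% |
| Keep half the benefit | 0.5 | 1.048 + 0.131 = 1.179 kg | 1.31 / 1.179 = 1.11, so about 11% |
| Change like controls | 0 | 1.048 kg | 1.31 / 1.048 = 1.25, so 25% |

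With k = 0 and a different loss, the difference is 0.90 × 1.31 = 1.179 kg at 10% (11%) and 0.70 × 1.31 = 0.917 kg at 30% (43%). If losses in both arms are equally frequent and shifted by the same amount, the shifts cancel and the bias is zero.

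**The case against.** Several points on the other side are sound.

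- **Scope of the sentence.** It directly follows the per-protocol definition and could be read as applying only there. This is possible but less likely: the per-protocol set already requires completion, the wording is general, and the article gives no other missing-data rule for the primary analysis.
- **Loose labelling.** The article explains intent-to-treat as ignoring compliance, and 24 evaluable per arm was planned for openly. The authors may simply have meant all randomised participants with an outcome. That would explain the label without justifying it, and a larger sample does nothing about selective loss.
- **Detail left to an analysis plan.** Imputation models commonly sit there, and their absence from an article is no fault. Here, however, the article states a rule, so a later plan using all randomised participants would have to overturn it.

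A reader might also infer that the primary result describes only those who tolerated and finished the biscuits, or that it differs from per-protocol only by the 80% threshold. The documents do not support either reading, because exclusion depends on a missing scan and not on stopping the product. Nor do they support a flat claim that the effect is overstated by 25%. That figure needs fibre-arm losses to match the control mean exactly, and also needs -1.11 kg to be the value among those observed. The expected loss is the same in both arms.

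**Conclusion.** The point holds as an inconsistency within one paragraph. As most naturally read, the primary analysis is an available-case analysis of randomised participants with a week-12 DXA, about 48 of 60 at the expected loss, under an intent-to-treat label. The count rests only on the plan's 20% and on the general reading of the exclusion sentence.

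Any effect on the estimate cannot be derived from the documents in either direction or size. The illustrated range at 20% loss, 0% to 25% overstatement, depends wholly on what is assumed about those lost and starts at zero. The sample size itself is not at fault. Severity: should-fix.

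**What to change.** Replace the exclusion sentence with a rule along these lines:

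- The primary analysis includes all randomised participants in their assigned arm.
- The week-12 DXA already scheduled is sought from everyone, including those who stop the product.
- Week-12 fat mass that is still missing is multiply imputed with a small model: arm, baseline fat mass, sex, age, and the latest available weight change from weeks 4, 8 or 12. With about 24 observed per arm, a long list of correlated weight and waist values would be unstable.
- A control-based imputation is added as a sensitivity analysis, because multiple imputation ordinarily assumes that data are missing at random given the variables in the model.
- The complete-case analysis is kept as a sensitivity analysis and labelled as such.

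The cost is revised wording and some extra programming, with no new visits or measurements. Two limits should be accepted: participants who leave before week 4 have no later weight to inform the imputation, and the estimate may be less favourable than the available-case one.

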### Specific objectives

This project proposes to perform a comprehensive investigation of the effects of pea fibre supplementation on 1) weight loss, 2) glucose control and features of the metabolic syndrome, 3) food intake and satiety, and 4) gut microbiota and serum and fecal water metabolites in free-living overweight and obese adults. The combination of anthropometric measurements with plasma metabolomics and analysis of fecal microbiota will provide unique information on the whole-body and *in vivo* effects of pea fibre consumption in overweight adults.

Given the research aims, the primary outcome is change in body fat mass from baseline to 12 weeks. Our secondary outcomes include glucose tolerance, serum lipids and inflammatory markers, and objective and subjective measures of food intake and appetite. To better understand the mechanisms by which yellow pea fibre may impact metabolism, we will also undertake exploratory mechanistic studies on changes in intestinal microbiota and *in vivo* metabolism assessed using metabolomics analysis.

It is first hypothesized that the group consuming the pea fibre will have a greater reduction in body fat compared to the control group. Second, it is predicted that at follow-up the pea fibre group will have lower fasting insulin concentrations and reduced glucose and insulin excursions during an oral glucose tolerance test (OGTT). Third, it is expected that the pea fibre group will have greater ratings of fullness and a reduction in *ad libitum* energy intake compared to control. Finally, it is anticipated that supplementation of pea fibre will beneficially alter gut microbiota and induce a unique serum and fecal water metabolite signature reflective of the changes in body fat mass.

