For analysis of gut bacteria species, total bacterial DNA will be extracted from the frozen fecal samples using the QIAamp DNA Stool Mini Kit (Qiagen, Mississauga, ON). Bacterial DNA concentrations will be measured using the Pico-Green DNA Quantification Kit (Invitrogen, Carlsbad, CA). Microbiota will be quantified using quantitative PCR according to our previous work [47] using the BioRad iCycler (BioRad Inc., Mississauga, ON) and group-specific primers. Briefly, amplification and detection will be conducted in 96-well plates with SYBR Green 2 × qPCR Master Mix (BioRad). Group specific primers have been previously published [47]. The 16S rRNA gene copies value will be calculated according the following webpage: http://cels.uri.edu/gsc/cndna.html using average genome sizes. Standard curves will be normalized to the copy number of the 16S rRNA gene obtained from the following webpage: http://rrndb.umms.med.umich.edu/.

#### **
*Serum metabolomics*
**

Metabolomics analysis provides a snapshot of an organism’s current metabolic profile. Beyond measurement of single metabolites, applying principal component analysis (PCA) to metabolomics data allows for the relationships between variables to be determined, thereby identifying a metabolic signature [48]. Sample preparation and metabolomics analysis will be performed according to our previous work [39]. Briefly, following sample preparation, including filtering and pH standardization, all NMR experiments will be performed on a Bruker Advance 600 spectrometer (Bruker Biospin, Milton, Canada). Processed spectra will be imported into Chenomx NMR Suite software (Edmonton, AB) for metabolite identification and quantification. In order to describe the metabolite changes in the context of other physiological variables, metabolomic data will be integrated with the other biological variables assessed (blood biochemistry, satiety hormones, body composition) using O2PLS-DA (orthogonal partial least squares discriminatory analysis) modeling [39,49].

#### **
*Fecal water metabolomics*
**

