The fecal samples collected at baseline and 12 weeks will be used for fecal water ^1^H-NMR metabolomic analysis. The NMR sample preparation protocol will be based on previously published work that has been shown to maximize retrieval of SCFAs from the fecal samples [50]. ^1^H-NMR spectra will be acquired on a Bruker Advance 600 spectrometer (Bruker Biospin, Milton, Canada) operating at 600.22 MHz, and multivariate analysis of metabolic profiles will be performed using SIMCA-P + 12.0.1 software (Umetrics). The PCA and O-PLS-DA models of the fecal water extracts are expected to show separation between the control and pea fibre groups based on metabolite concentrations involved in gut microbiota activity resulting from fibre fermentation.

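### The supervised metabolite models all take diet as outcome, so the hypothesised link with fat loss is untested, and in-sample separation of the arms would appear even under no effect (low severity, exploratory)

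*Protocol article*

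**What the plan says.** All references are to the protocol article.

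- **Specific objectives.** The final hypothesis has two parts: a beneficial change in gut microbiota, and that fibre will "induce a unique serum and fecal water metabolite signature reflective of the changes in body fat mass". The same section labels the mechanistic work exploratory: "we will also undertake exploratory mechanistic studies on changes in intestinal microbiota" and on in vivo metabolism.
- **Statistical analysis.** "For metabolomics analysis, in addition to univariate tests, multivariate analysis will conducted using SIMCA-P + 12.0.1 software". The models are then listed. First, "A supervised partial least squares discriminant analysis (PLS-DA) approach will be used to compare the variance of metabolite concentrations between the two sample classes", the classes being the two diets. Second, "A supervised orthogonal partial least squares analysis will be used (control versus pea fibre) for a direct comparison", with diet type as Y and metabolite concentrations as X. Third, an O2-PLS-DA that pools metabolites with satiety hormones and other biological measurements and again takes diet type as the outcome.
- **Serum metabolomics.** Body composition is named among the variables to be integrated with the metabolites by O2PLS-DA. Method details are deferred: "Sample preparation and metabolomics analysis will be performed according to our previous work".
- **Fecal water metabolomics.** "The fecal samples collected at baseline and 12 weeks will be used for fecal water" NMR analysis, and "The PCA and O-PLS-DA models of the fecal water extracts are expected to show separation between the control and pea fibre groups".

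**The concern.** There are three linked difficulties.

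1. **Aim and model do not match.** The hypothesis ties the metabolite signature to change in fat mass, but every supervised model has diet as its outcome.
2. **The expected result does not discriminate.** PLS-DA and O-PLS-DA use the arm labels to find the directions that best separate the arms. With dozens of variables and 24 to 30 people per arm, such a direction exists in any data set, including one where fibre does nothing.
3. **The role of baseline is left open.** The stated interest is in changes, but the models are described in terms of concentrations in two diet classes. Week 12 alone, both visits pooled, or within-person change would all fit the text.

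At stake is how the mechanistic results are read. A metabolite signature could be reported from a fitted plot when there is none, and its connection with fat loss could be asserted without having been examined.

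**Working it through.** **Sample size.** From Sample size calculation: difference 1.11 + 0.20 = 1.31 kg, SD 1.6 kg, two-sided alpha 0.05, power 0.80.

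n per arm = 2 × (1.960 + 0.842)² × 1.6² / 1.31² = 2 × 7.85 × 2.56 / 1.716 = 23.4, so 24. With 20% loss, 24 / 0.80 = 30. Both of the article's figures reproduce. They serve here only as the number of people available to the metabolite models.

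**Aim against models.**

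| Model | Outcome (Y) | Predictors (X) | Relates metabolites to fat change? |
|---|---|---|---|
| PLS-DA | diet class | metabolites | no |
| OPLS | diet type | metabolites | no |
| O2-PLS-DA | diet type | metabolites, satiety hormones, other measures (body composition per Serum metabolomics) | not directly |

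In the third model, metabolites and fat mass can both load on the diet axis because each differs between arms on average. That can happen when, within arms, people whose metabolites changed most did not lose more fat. Conversely, a real metabolite-fat association unrelated to diet need not appear on that axis. Shared loading is therefore not a test of the hypothesis.

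**Separation under no effect: closed form.** Assume p independent, unit-variance noise variables and n people per arm. The first PLS direction is proportional to the vector of between-arm mean differences, each with variance 2/n. Along it the fitted arms lie about √(2p/n) apart with within-arm SD about 1, so in-sample AUC ≈ Φ(√(2p/n)/√2) = Φ(√(p/n)). At n = 30:

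- p = 20: Φ(0.816) = 0.79
- p = 40: Φ(1.155) = 0.88
- p = 100: Φ(1.826) = 0.97
- p = 200: Φ(2.582) = 0.995

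The true AUC is 0.50 in every case.

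**Separation under no effect: simulation.** Pure noise, unit-variance scaling, 200 data sets per setting, variables independent or correlated (parameter 0.5). In-sample AUC at 30 per arm with 1, 2 and 3 components:

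| Variables (assumed) | Independent | Correlated |
|---|---|---|
| 20 | 0.79, 0.83, 0.84 | 0.74, 0.80, 0.82 |
| 40 | 0.88, 0.93, 0.96 | 0.78, 0.88, 0.92 |
| 100 | 0.97, 1.00, 1.00 | 0.81, 0.96, 0.99 |
| 200 | 1.00, 1.00, 1.00 | 0.82, 0.98, 1.00 |

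The one-component independent column agrees with the closed form. Values at 24 per arm are slightly higher. A t-test of first-component scores between arms gave P ≤ 0.05 in 98.5 to 100% of noise data sets, so the article's significance level gives no protection if applied to fitted scores.

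A separate simulation (300 data sets, 24 per arm, 50 noise variables, two components) gave 93% apparent correct classification for independent variables and 87% with ten shared factors. Cross-validated accuracy was 49% and 47%.

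**The same noise under validation.** Q2 = 1 − (cross-validated prediction sum of squares)/(total sum of squares of Y). With seven folds, accuracy was 47 to 50% and mean Q2 was negative in every setting (−0.22 to −1.12). Q2 still exceeded zero in 0.5 to 15.5% of noise data sets, so that criterion alone can be too lenient, and a permutation test is needed beside it.

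**Baseline.** Fecal samples from both visits are analysed. Blood is also drawn at both, although the serum section does not name the visits for metabolomics. A week-12 comparison is valid under randomisation but carries chance baseline differences. Pooling visits would place unexposed baseline samples in the pea fibre class. Within-person change avoids both problems.

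**The case against.** The strongest reply is that this is a condensed article on exploratory work. Cross-validation folds, Q2 thresholds and permutation counts commonly sit in a full protocol or SAP, and the article refers its metabolomics method to earlier work that is not shown. That stands: silence on validation does not show that none is planned, and the point does not rest on it.

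A reader might also infer more than the text supports:

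- **That fitted separation is the decision rule.** It is stated as an expectation only. It covers PCA, which does not use the arm labels and is not subject to this overfitting, and univariate tests are planned as well. The Background also reports an earlier fibre trial in which no clear clustering by treatment was found, so the authors know that separation may fail to appear.
- **That baseline samples go unused.** The fecal water section says the opposite. What is open is how they enter the two-class models.
- **That the whole final hypothesis would be confirmed under no effect.** It also covers gut microbiota, which is measured by quantitative PCR and is outside these models.
- **That separation on noise is guaranteed to be near complete.** It depends on the numbers of variables and components, neither of which is given.

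The planned joint model with body composition is a fair partial answer on the fat-mass link, but its outcome is still diet type. The mismatch between aim and model is in what the article states, not in what it omits.

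**Conclusion.** The point holds at low severity. As described, no supervised model tests whether the metabolite signature tracks change in body fat. The expected separation, where it comes from a fitted supervised model, would be seen with or without an effect: in-sample AUC of about 0.74 to 1.00 at 24 to 30 per arm, against chance accuracy under cross-validation. That range assumes 20 to 200 variables, one to three components and unit-variance scaling as planned. Near 20 variables the separation is only partial. How baseline enters the diet models needs stating. The primary outcome, the secondary outcomes and the sample size are unaffected.

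**What to change.** 1. Add an OPLS regression with each participant's change in fat mass (week 12 minus week 0) as outcome and metabolite changes over the same interval as predictors. Validate it by cross-validation and by permuting the fat-mass changes. The result is an association, not proof of mediation.
2. State that the diet models use baseline-referenced metabolite data, such as week 12 minus week 0.
3. State that a signature will be claimed only if cross-validated Q2 exceeds zero and a label-permutation test gives P of 0.05 or less, and not from separation in a fitted score plot. If the SAP or the cited earlier work already holds such a rule, a reference to it is enough.

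Rewording the sentence that expects separation is optional.

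The cost is a little more computing on data already being collected. The downside is that an apparent separation may not survive validation.
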